### Analysis

Analysis will be done using the Data Analysis and Statistical Software: STATA, version 14 with an alpha of 0.05 set a priori. We will summarize the baseline data by group assignment using descriptive statistics: means and SD will be used for continuous data with normal distribution, medians, and interquartile range for skewed data, and percentages for categorical data. Our primary outcome, physical activity, measured longitudinally over 6 months, will be assessed by mixed-model analysis of variance with intervention assignment as between-group factor and time as within-subject factor. Continuous data will be compared between control and intervention groups using the *t* -test or the Wilcoxon Mann-Whitney test and the categorical variables will be compared using the chi-square test. All analyses will be based on intention-to-treat in all randomized patients.

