**Methods:**

The study will be implemented as a 2-arm randomized controlled trial with 300 adult patients with chronic conditions over a 6-month follow-up period. Participants will be assigned to either the intervention group receiving the FeatForward app and standard care versus a control group who will receive only usual care. The difference in physical activity levels between the control group and intervention group will be measured as the primary outcome. We will also evaluate the effect of this intervention on secondary measures including clinical outcome changes in global CMR factors (glycated hemoglobin, fasting blood glucose, blood pressure, waist circumference, Serum lipids, C-reactive protein), health-related quality of life, health care usage, including attendance of scheduled clinic visits and hospitalizations, usability, and satisfaction, participant engagement with the FeatForward app, physician engagement with physician portal, and willingness to engage in physical activity. Instruments that will be used in evaluating secondary outcomes include the Short-Form (SF)-12, app usability and satisfaction questionnaires, physician satisfaction questionnaire. The intention-to-treat approach will be used to evaluate outcomes. All outcomes will be measured longitudinally at baseline, midpoint (3 months), and 6 months. Our primary outcome, physical activity, will be assessed by mixed-model analysis of variance with intervention assignment as between-group factor and time as within-subject factor. A similar approach will be used to analyze continuous secondary outcomes while categorical outcomes will be analyzed by chi-square test.

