### Specific Aims

Our primary aim is to evaluate the effect of FeatForward on physical activity levels. Secondary outcomes to be assessed include evaluating the effects of FeatForward on: (1) clinical outcomes by measuring changes in global CMR factors (HbA1c, fasting blood glucose, blood pressure (BP), waist circumference (WC), serum lipids, C-reactive protein (CRP)), (2) health-related quality of life, (3) health care usage, including attendance of scheduled clinic visits and hospitalizations, (4) usability and satisfaction with FeatForward, (5) participant engagement with FeatForward, and (6) physician engagement with the FeatForward physician portal, (7) continuum of behavioral regulation in exercise.

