### Outcomes Measurement

The difference in physical activity levels between the control group (smartphone with sHealth app, smartwatch, and routine medical care) and intervention group (smartphone with FeatForward app, smartwatch, routine medical care) will be measured as the primary outcome of interest for this study. The participants will track physical activity using the activity trackers provided.

All secondary outcomes will be assessed at enrollment, midpoint, and at the end of the study. Body weight is measured with participants dressed in light clothing and without shoes to the nearest 0.1 kg with a validated digital scale. Changes in global CMR factors are assessed in the following ways: measurement of fasting glucose level, HbA1c, and serum lipids will occur in a standard laboratory by fasting venous blood samples collected by at baseline, the midstudy visit, and at the final study visit. Phlebotomy is performed by research nurses who will adhere to standard institutional guidelines. Additionally, high sensitivity CRP is measured at the initial visit and final study visit. BP is measured by validated automated digital BP monitors and is performed by nurses who will adhere to standard BP measurement guidelines based on American Heart Association guidelines. At each visit, the participant’s BP will be established by a minimum of two BP measurements taken at least 5 minutes apart, and the average of these readings will represent the participant’s BP. If there is greater than 5 mm Hg difference between the first and second readings, an additional reading will be obtained, and then the average of these three readings will be used to represent the participant’s BP. WC is measured at the midpoint between the iliac crest and the lowest rib. Two measurements are taken following expiration and the average of these readings will represent the participant’s WC. If there is greater than 1-cm difference between the first and second measurements, an additional measurement will be obtained, and then the average of these three measurements is used to represent the participant’s WC.

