A clustered cardiometabolic risk (CCMR) score will be constructed by summing *z* scores (units of standard deviation (SD) from the population mean) of baseline values for WC, systolic blood pressure (SBP), fasting blood glucose, serum lipids, weight, HbA_1c_, using sex-specific baseline means and SDs (CCMR = (value − mean)/SD), from which *z* scores of the follow-up variables will be computed. We will divide both the mean and SD by 6, separately, to account for the number of variables included. Change in the CCMR will be calculated by subtracting the follow-up CCMR from the baseline CCMR [10]. In addition, all the CMR factors will be evaluated individually to assess the effect of the app on each of the risk factors.

The health-related quality of life will be assessed using a validated questionnaire (short form (SF)-12). Health care usage will be assessed by emergency department visits, attendance of scheduled visits and inpatient hospitalizations. These usage data will be collected from the Partners Healthcare’s Research Patient Data Registry (RPDR) at the end of the study. The RPDR is the centralized clinical data warehouse that operates under Partners Research Information Services. It securely stores all data from across Partners hospital systems in one place, and ensures security and confidentiality of patient information [11].

Usability and satisfaction will be assessed at close-out via questionnaires specifically designed for this project. Participant engagement will be measured via app usage data including overall frequency of use, frequently visited pages, time spent on these pages, responses to messages and user entries (weight, BP, glucose, heart rate). Lastly, physician engagement will be measured via time logged in the physician portal and questionnaire designed to measure portal satisfaction *.*

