### Statistical Analysis Plan

#### Sample Size Estimation

A total of 300 patients (150 participants per group) will be recruited for this study. There is an 80% probability that the study will detect a treatment difference at a two-sided 0.05 significance level, if the true difference in mean step counts between the control arm and the intervention arms is 1000 steps/day. This is based on the assumption that the SD of the response variable is 2750 and accounting for an attrition rate of 20%. Participants will be followed up for a total of 6 months.

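### The Abstract and the Analysis section give different analyses for the continuous secondary outcomes measured at baseline, 3 and 6 months

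*Protocol article*

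**What the plan says.** The Methods paragraph of the Abstract describes a mixed-model analysis of variance for physical activity and continues: "A similar approach will be used to analyze continuous secondary outcomes while categorical outcomes will be analyzed by chi-square test".

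The Analysis section says that the primary outcome "will be assessed by mixed-model analysis of variance with intervention assignment as between-group factor and time as within-subject factor". Its next sentence reads: "Continuous data will be compared between control and intervention groups using the" *t*-test or the Wilcoxon Mann-Whitney test, with chi-square for categorical variables. It closes with: "All analyses will be based on intention-to-treat in all randomized patients".

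Three other places bear on the point:
- Outcomes Measurement on timing: "All secondary outcomes will be assessed at enrollment, midpoint, and at the end of the study".
- Specific Aims and Outcomes Measurement on change from baseline: the aims speak of "clinical outcomes by measuring changes in global CMR factors", and for the clustered cardiometabolic risk (CCMR) score, "Change in the CCMR will be calculated by subtracting the follow-up CCMR from the baseline CCMR".
- Sample Size Estimation, which sets 300 patients "accounting for an attrition rate of 20" percent.

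**The concern.** The two statements have the same structure: mixed model for the primary outcome, then a method for continuous outcomes, then chi-square for categorical ones. Only the middle element differs. A mixed model uses several visits per patient; a two-sample test compares one quantity at one visit. Applied to the same data they can give different estimates and p-values.

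The affected outcomes are the cardiometabolic risk (CMR) factors (HbA1c, fasting glucose, blood pressure, waist circumference, lipids, C-reactive protein), the CCMR score, the SF-12 and the exercise-regulation questionnaire. While both methods stand, either can be reported for any of these and still be called planned. If the two-sample version is followed, precision may also be lost and patients without a month-6 value fall outside the test.

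**Working it through.** **1. The plan's own figure.** Inputs from Sample Size Estimation: difference 1000 steps/day, SD 2750, two-sided 0.05, power 80%, attrition 20%.

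n per arm = 2 × (1.960 + 0.842)² × (2750/1000)² = 118.7, so 119. Inflated: 119 / 0.80 = 148.75, so 149 per arm and 298 in total. The stated 300 reproduces. With 150 × 0.80 = 120 completers per arm, power is 80.4%. No stated figure is in dispute.

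**2. The two statements side by side.**

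| | Abstract | Analysis section |
|---|---|---|
| Primary outcome | mixed-model ANOVA | mixed-model ANOVA |
| Continuous, other | similar to the primary | *t*-test or Wilcoxon |
| Categorical | chi-square | chi-square |
| Visit tested | not named | not named |
| Quantity tested (follow-up value or change) | not named | not named |

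Baseline data already have their own sentence in the Analysis section, with descriptive summaries. The *t*-test sentence comes after the primary model and just before the intention-to-treat statement. It most naturally covers outcomes.

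**3. Precision if the two-sample test is meant.** Let r be the correlation between baseline and follow-up. The document gives none, so r is an assumption and a range is shown. With equal variances at both visits, and the variance of a follow-up-only comparison set to 1:
- change score: 2(1 − r)
- baseline-adjusted (ANCOVA): 1 − r²

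Relative to the adjusted analysis, a test on follow-up values has variance 1/(1 − r²). A test on change scores has 2(1 − r)/(1 − r²) = 2/(1 + r).

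| r (assumed) | Follow-up values vs adjusted | Change scores vs adjusted |
|---|---|---|
| 0.3 | 1/0.91 = 1.10 | 2/1.3 = 1.54 |
| 0.5 | 1/0.75 = 1.33 | 2/1.5 = 1.33 |
| 0.7 | 1/0.51 = 1.96 | 2/1.7 = 1.18 |
| 0.8 | 1/0.36 = 2.78 | 2/1.8 = 1.11 |

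As smallest detectable differences in SD units (120 per arm, 80% power, two-sided 0.05), a follow-up-only test gives (1.960 + 0.842) × √(2/120) = 0.36. The others multiply this by √(2(1 − r)) or √(1 − r²):

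| r (assumed) | Follow-up values | Change scores | Adjusted |
|---|---|---|---|
| 0.3 | 0.36 | 0.43 | 0.35 |
| 0.5 | 0.36 | 0.36 | 0.31 |
| 0.7 | 0.36 | 0.28 | 0.26 |
| 0.8 | 0.36 | 0.23 | 0.22 |

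**4. Patients in a month-6 test.** 20% of 300 = 60 without a month-6 value, leaving 240. This applies the planned attrition to the secondary outcomes and assumes no imputation.

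**The case against.** The strongest reply is that the Analysis section never mentions secondary outcomes. Its sentence could cover baseline comparisons, or measures with no repeated assessment, such as health care usage extracted from the registry at the end of the study. A two-sample or rank test is ordinary there. The second reading has some force, and the fix keeps those tests for such measures. But the sentence is not limited in that way. If it were, the Analysis section would give no method for the three-visit outcomes, and the text would still need correcting.

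A reader might infer that the Analysis section ignores the measured baseline. The documents do not support that. No tested quantity is named, and the aims and the CCMR definition speak of change, which uses baseline. For a test on change scores the precision loss shrinks as r rises, so the ratios 1.96 and 2.78 belong to the follow-up-only reading alone.

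A reader might also infer that patients lost to follow-up will be dropped. The article states neither exclusion nor imputation, and missing-data handling may sit in a fuller plan that is not shown. Only the conditional tension with the intention-to-treat statement remains.

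Two further points stand. The Abstract's model names no baseline covariate. If baseline is one of its time levels, its month-6 arm-by-time contrast with complete data is in essence a change-score comparison. Against a follow-up-only test its variance is then equal at r = 0.5 and 2(1 − 0.3) = 1.4 times as large at r = 0.3. The Abstract's version is therefore not automatically the more precise one. And the choice between *t*-test and Wilcoxon is no separate fault: the same paragraph distinguishes normal from skewed data for summaries, and an exact rule can be left to an analysis plan.

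**Conclusion.** The contradiction holds: the article states two different methods for the continuous secondary outcomes measured at three visits. This rests on the wording alone, with no numerical assumption, although the Analysis section has to be read as covering outcomes.

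The consequences are conditional on the two-sample test being meant. The variance penalty against a baseline-adjusted analysis is then 1.33, 1.96 and 2.78 for follow-up values, or 1.33, 1.18 and 1.11 for change scores, at assumed r = 0.5, 0.7 and 0.8. About 60 of 300 randomised patients would be absent from a month-6 test if nothing is imputed. The sample size and the primary analysis, which both places state alike, are unaffected. It should be corrected, but it concerns secondary outcomes only.

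**What to change.** Make the Abstract and the Analysis section agree. In the Analysis section, state that continuous secondary outcomes measured repeatedly (CMR factors, CCMR score, SF-12, exercise-regulation questionnaire) are analysed by a mixed model with arm, visit, arm-by-visit and the baseline value as covariate. It should use all available follow-up visits and report the month-6 adjusted difference with 95% CI. Where there is no month-3 value, use month 6 only. This may apply to C-reactive protein, which Outcomes Measurement places at the first and last visits while Table 1 also marks 3 months.

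Keep the *t*-test or Wilcoxon test only for continuous measures without repeated assessment, such as health care usage extracted once at the end of the study.

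Under the assumptions above, this model is at least as precise as either two-sample version. It keeps patients who have only a month-3 value and removes the choice between analyses. Patients with no follow-up value at all still contribute nothing to it, so the intention-to-treat sentence should be worded accordingly. Log transformation of skewed variables and multiple imputation are optional additions.

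The cost is a change of wording and modest programming, with no new data. It should be settled before the analysts are unblinded.

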### Ethics and Informed Consent

Procedures of our methods have been reviewed and approved by the IRB and the study is registered at clinicaltrials.gov [NCT02551640]. The app is secure and complies with all Health Insurance Portability and Accountability Act Regulations requirements. Subjects will require a secure pass code to be able to access the app. However, if any data breach or adverse event occurs, the investigator will ensure that they are well-documented and reported according to the IRB’s requirements, regardless of causality.

For those who attend the enrollment visit, a member of the research staff will review the informed consent form with them. Details of the study, including the purpose, procedures, and expected duration will be explained to the candidate participant. Study staff will clearly communicate that the participant’s participation or nonparticipation will not affect their medical care, and that they have the right to withdraw from the study at any time. Candidate participants will be given an opportunity to ask questions about the study, and they will be informed of their right to withdraw from the study at any time. The candidate participant may then voluntarily sign and date the informed consent form, thereby providing study staff permission to enroll them in the study if they meet all inclusion criteria. If for any reason the candidate participant desires more time to consider the decision, they will be provided a copy of the unsigned consent form for reference and instructed to call the study phone number if they decide to participate in the study. All participants who sign the consent form and are screened will be documented on a screening log. All enrolled participants will be assigned a unique study identification number, and a note will be made in the source documentation verifying that the participant has willingly signed the consent form prior to participation in any study procedures in the enrollment log.

## Results

The study is still in progress and we hope to have the results by the end of 2016.

## Discussion

### Trial Implications

The study examines how to creatively apply a mHealth technology to increase and maintain physical activity in patients with chronic diseases. Our expectation is that engaging patients to take charge of their health and empowering them with essential information will lead to improved health outcomes and quality of life. The FeatForward mobile app mimics a health coach to help engage users and increase their physical activity through education, tracking, feedback, and social network. The mobile app also features a physician-facing portal, which will serve as a channel of communication between the physicians and patients to improve the overall health outcomes.

Sedentary behavior and physical inactivity have been associated with increased risk for chronic diseases [1]. In addition to being the most common CMR, physical inactivity also happens to be the easiest to target [1]. A study by Lamb and colleagues [3] found that increasing the amount of time spent being physically active and decreasing the time spent sedentary may be an important strategy for self-management of chronic diseases such as diabetes early in the course of the disease. In recent times, several patient-centered interventions have been used to engage users and help them increase their level of physical activity, thereby improving the health outcomes over time. Such interventions use mobile apps and employ a range of features including providing feedback based on physical activity tracking, providing motivational messages, demonstrating the right way to exercise, setting and monitoring personalized goals, incorporating social media, and helping users schedule their exercise regimes [7].

A trial evaluating a mobile phone app, MyBehavior, designed to track physical activity and eating behavior data with personalized feedback demonstrated that the app was associated with increased physical activity [10]. Furthermore, a recent study by Block [14] used a fully automated, algorithm-driven behavioral intervention, Alive-PD, delivered via the Web, mobile phone, and automated phone calls for diabetes prevention. The intervention was associated with improved glycemic control, and decreased body weight, BMI, WC, triglycerides/high-density lippoproteins ratio, and diabetes risk [14].

While data demonstrating the positive impact of mobile health on clinical outcomes is growing, there is however mixed evidence of the impact of digital health technologies on health care costs. Results from a recent study by Bloss et al [15] concluded that there are no differences in health care costs or usage outcomes in patients using mHealth technologies for management of chronic diseases compared with a control group that received a standard disease management program [15]. Another study, a systematic literature review *of the cost-utility and cost-effectiveness of telemedicine and mHealth systems,*  reported mixed effect that s *ome studies demonstrated that telemedicine can reduce the costs while some others showed no impact on the health care cost reduction [16].* On the other hand, a meta-analysis of 11 randomized controlled trials including 5702 patients with heart failure showed that remote monitoring facilitated by electronic devices was associated with significant decreases in health care usage and costs [17]. With capabilities such as real-time remote monitoring of patients and data sharing with care providers, digital health technologies allow early intervention for high-risk patients in need of attention and thereby prevent unforeseen health care expenses [17]. Literature on cost effectivess of mHealth technologies is sparse and further research is warranted to demonstrate the impact of mHealth applications on cost and usage outcomes in the management ofchronic diseases.

The FeatForward app features a care provider portal integrated with the EMRs that allows physicians to monitor the patients’ progress and intervene when appropriate. We believe that early intervention by care providers will lead to a decrease in the number of emergency department and unscheduled clinic visits, thereby decreasing health care costs in the long run. Furthermore, mHealth technologies foster patient engagement for self-care and enhance their knowledge about their conditions to help them make informed health care decisions. Thus, these informed patients have better outcomes than uninformed patients [16,18]. The FeatForward app provides participants with an unrestricted access to a comprehensive library with information regarding a wide range of topics that are relevant to their health. We believe that increasing participants’ awareness of their conditions will help them better manage their illnesses and lead to improved outcomes.

### Limitations

An important limitation is that the FeatForward app is designed to support only android devices for this trial. This is important because a sizeable proportion of the US population own Apple operating system (iOS) devices and this can potentially affect the study’s accrual rates. While there is no robust data about the differences in demographics or the dynamics of user preferences of iOS versus Android users, early reports suggest that loyalty rates are usually high among users of either platform. Therefore, we speculate that some eligible iOS users may be reluctant to switch to Android for the duration of the study. Additionally, the impact of this limitation on the study’s generalizability is yet to be determined but we do not envisage any significant differences in the demographics of people using either of the platforms. Despite these limitations, this study demonstrates the potential of using personalized messages and activity tracking to deliver a theory-driven intervention to users. As we move into a time where increasingly more people are employing technology to monitor their health, we believe that FeatForward holds great promise in increasing disease knowledge and improving health outcomes.

